## Methods/design

### Trial organization/coordination

This study is designed as an open-label, prospective, single-center, randomized two-armed (carbon ion radiotherapy vs. simultaneous integrated boost radiotherapy) study, primarily evaluating the differences in the severity and incidence of acute toxicity in patients with localized prostate cancer treated with carbon ion radiotherapy and simultaneous integrated boost carbon ion radiotherapy and further optimizing carbon ion therapy for prostate cancer. The rationale for this SIB approach is to provide a greater overall tumor-killing effect to prolong the biochemical recurrence-free survival without additional toxicity as compared with standard treatment. The two study arms are defined by different treatment strategy with arm A (carbon ion radiotherapy at 65.6 Gy in 16 fractions) and arm B (SIB carbon ion radiotherapy to the imaging-visible malignancy at 72Gy in 16 fractions). The flow chart of this phase II trial is illustrated in Fig. 1. The study carries out in Shanghai Proton and Heavy Ion Center (SPHIC) in China, and ethical consent was obtained from the ethics committee of SPHIC before trial initiation. The number of the ethics committee of SPHIC (Institutional Review Board) is 2006-62-03. All patients have written informed consent before inclusion in the trial.

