### Statistical analysis

The primary endpoint of the study is to observe the difference in acute toxicity in patients with localized prostate cancer who receive carbon ion radiotherapy and SIB carbon ion radiotherapy. All the patients will be randomly assigned to arm A and arm B in a ratio of 1:1. Assuming a type I error of 0.025 and type II error of 0.2, and under the assumption that the probability of no more than 2 degrees of acute GU and GI toxicities in arm A is 90% (Pc), and the probability of no more than 2 degrees of acute GU and GI toxicities in arm B is also 90% (Pt), with a non-inferiority margin of 0.15, we estimate that a sample size of 63 participants per arm will yield 80% power to show non-inferiority. However, anticipating a possible 10% dropout rate in each group, per arm *n* = 70 patients will be recruited into the study such that a total of *N* = 140 patients is required.

Statistical analysis will be performed using SPSS software (V20.0, SPSS Inc., Chicago, IL, USA). The Mann-Whitney *U* test will be used to compare the differences in acute and late toxicity between the two arms. The Kaplan-Meier method will be used to estimate the biochemical relapse-free survival, progression-free survival, and overall survival of the entire cohort. The association between each of the candidate prognostic factors with biochemical relapse-free survival, progression-free survival, and overall survival rates will be tested using the log-rank test. Multivariate analysis will be performed using the Cox regression model.

Analysis is planned on an intention-to-treat population (ITT), with all participants to be analyzed in the group to which they were randomized. We will make efforts to collect complete data for all participants and minimize missing data. If required, the missing data will be dealt with last observation carried forward method or multiple imputation.

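### The trial is sized to show non-inferiority of a toxicity proportion with a 0.15 margin, but the only test named for acute toxicity is a Mann-Whitney test of differences that does not use the margin

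*Protocol article*

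**What the plan says.** All of this is in the protocol article.

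- **Design.** The Statistical analysis section opens its calculation with "Assuming a type I error of 0.025 and type II error of 0.2". It assumes the same 90% probability of an acceptable toxicity outcome in both arms, and continues: "with a non-inferiority margin of 0.15, we estimate that a sample size of 63 participants per arm will yield 80% power to show non-inferiority". A 10% dropout allowance takes this to 70 per arm, 140 in total.
- **Analysis.** The next paragraph of that section gives the only analysis for acute toxicity. The Mann-Whitney U "test will be used to compare the differences in acute and late toxicity between the two arms". The margin is not mentioned again, and no confidence interval, non-inferiority test or decision rule is stated.
- **Endpoint.** The Abstract (Methods) and Duration of the study define the primary endpoint as acute toxicity of grade 2 or higher, and the Abstract calls it an incidence. The sample-size text instead works with "the probability of no more than 2 degrees of acute GU and GI toxicities in arm A is 90% (Pc").
- **Aim.** Trial organization/coordination states the aim as differences in both severity and incidence, and gives the rationale for the boost as a stronger tumour effect "without additional toxicity as compared with standard treatment".

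**The concern.** The design and the analysis ask different questions. The sample size is for rejecting the hypothesis that the boost arm is worse by 15 points or more. The Mann-Whitney test has equality of the arms as its null hypothesis. Failing to reject equality does not show that an excess of 15 points has been excluded; it may only mean that the trial is small.

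The scale may differ as well. The margin is defined on a proportion, whereas a Mann-Whitney test on toxicity would naturally rank the full grade scale.

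What is at stake is the claim for which the trial was powered. If the report follows the analysis paragraph, it will give a p-value for a difference, and a non-significant one could be taken to mean that the boost adds no toxicity. That inference would not have the 2.5% error control built into the design.

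**Working it through.** **1. Reproduce the plan's sample size.** Inputs from Statistical analysis: Pc = Pt = 0.90, margin 0.15, type I error 0.025, power 0.80, allocation 1:1.

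n per arm = (z₀.₉₇₅ + z₀.₈₀)² × [Pc(1 − Pc) + Pt(1 − Pt)] / margin²
= (1.960 + 0.842)² × (2 × 0.9 × 0.1) / 0.15² = 62.8, rounded up to 63.

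63 / (1 − 0.10) = 70 per arm, so N = 140. Both figures match. The text does not give the sidedness, but one-sided 0.025 gives 63, while one-sided 0.0125 gives 77 and one-sided 0.05 gives 50. The design is therefore a one-sided 0.025 non-inferiority comparison of two proportions, and its arithmetic is correct.

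**2. What the named test does under that design.** Two assumptions are needed, because the article states neither: the test is two-sided at 0.05, and it is applied to the dichotomised endpoint. On binary data with n per arm, N = 2n and pooled event proportion p̄, the tie-corrected Mann-Whitney statistic is

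z = (p_B − p_A) / √[p̄(1 − p̄) × (2/n) × N/(N − 1)].

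Summing exact binomial probabilities over all outcomes gives:

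| True event rates, A vs B | n per arm | Significant | Not significant |
|---|---|---|---|
| 10% vs 10% (design assumption) | 63 | 5.1% | 94.9% |
| 10% vs 10% | 70 | 5.1% | 94.9% |
| 10% vs 25% (exactly at the margin) | 63 | 60.6% | 39.4% |
| 10% vs 25% | 70 | 66.2% | 33.8% |

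At the design assumption the test is significant about 5% of the time, as any test of equality should be when the arms are equal, so the 80% power is not a property of it. At the margin, reading a non-significant result as non-inferior would be wrong in 39% or 34% of trials.

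**3. What a margin-based rule does.** Compare the upper limit of the two-sided 95% interval for p_B − p_A with 0.15, by the same enumeration.

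| Interval | Power at 10% vs 10%, n = 63 | n = 70 |
|---|---|---|
| Wald | 80.7% | 84.2% |
| Newcombe | 77.0% | 80.4% |
| Miettinen-Nurminen | 73.7% | about 80% |

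At 10% vs 25%, the false non-inferiority rate is 2.9% for Wald at either size, and 2.6% (n = 63) or 2.5% (n = 70) for Newcombe.

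**4. One hypothetical result, both ways.** Events in 6/63 (9.5%) in arm A and 12/63 (19.0%) in arm B.

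- Mann-Whitney: p̄ = 18/126 = 0.143; z = 0.0952 / √(0.1224 × 2/63 × 126/125) = 0.0952 / 0.0626 = 1.52; p = 0.13, not significant.
- Wald interval: standard error = √[(0.0952 × 0.9048 + 0.1905 × 0.8095)/63] = 0.0618; upper limit = 0.0952 + 1.96 × 0.0618 = 0.216. Newcombe gives 0.220.

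Both upper limits exceed 0.15. The named test finds no significant difference, yet non-inferiority is not shown.

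**The case against.** **A condensed article may leave the interval to the analysis plan.** The interval method could well be there. But the article does more than stay silent: it names a test for the primary endpoint, and that test conflicts with the design. A later document would have to carry the conflict forward or contradict the article.

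**Mann-Whitney has a proper use here.** This stands. Severity is part of the stated aim, in the Abstract's Discussion and in Trial organization/coordination, and the sentence covers acute and late toxicity together. A rank test on ordered grades is reasonable for severity. The fault is that it is the only test named for an endpoint sized on a proportion with a margin.

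**A reader might infer that the primary question cannot be answered.** The documents do not support that. The margin, error rates and non-inferiority aim are stated, the toxicity data will be collected, and the interval can be computed from them.

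**A reader might take 34–39% as the trial's error rate.** That also goes too far. The figure assumes a two-sided 0.05 test, a dichotomised outcome, and non-significance read as non-inferiority. The article states no such decision rule, and the phrase about no additional toxicity is a rationale, not a planned conclusion.

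**The 10% event rate is not secure.** This stands too. Read literally, the sample-size wording makes 10% the rate of grade 3 or higher, while the endpoint is grade 2 or higher. The arithmetic above holds for an event with a 10% rate, whichever it is, but the margin cannot be applied until the event is settled.

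**Conclusion.** Wrong as written, and it must be fixed. The sample size is correct for a one-sided 0.025 non-inferiority comparison of proportions, but the only analysis named for acute toxicity tests a difference, ignores the 0.15 margin and does not have the stated 80% power to show non-inferiority.

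That conclusion does not depend on whether grades or a binary outcome are ranked, or on the test level, because the margin enters in neither case. The 39% and 34% figures do depend on the assumptions set out above and only illustrate what could follow if a non-significant result were taken as non-inferiority.

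**What to change.** 1. **Reconcile the event definition.** Align the sample-size wording (no more than grade 2) with the endpoint in the Abstract and in Duration of the study (grade 2 or higher), and confirm that the 90% assumption refers to the event chosen.
2. **State the primary analysis.** Estimate the arm B minus arm A difference in the proportion with that event, with a two-sided 95% confidence interval by one pre-named method. Declare non-inferiority only if the upper limit is below 0.15.
3. **Keep Mann-Whitney on grades** as a supportive analysis of severity.
4. **Word the conclusion to match.** A positive result excludes an excess of 15 points or more; it does not show that there is no additional toxicity.
5. **State the power for the method chosen.** At 63 and 70 evaluable per arm it is about 81% and 84% (Wald), 77% and 80% (Newcombe), or 74% and 80% (Miettinen-Nurminen). With either of the last two, 80% is reached at 70 evaluable, not at 63.

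Stratifying by risk group is not needed to cure the mismatch. At a 10% rate there would be about 6 events per arm (0.10 × 63 = 6.3) to spread over the strata.

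The cost is wording only, with no new patients or data. The Protocol amendments section requires a formal amendment and Institutional Review Board approval for important changes to analyses, so the change should go through that route.

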### Outcome measures

The primary objective of this phase II randomized study is to evaluate the differences of acute toxicities in patients with localized prostate cancer treated with carbon ion radiotherapy and SIB carbon ion radiotherapy.

Late toxicities, biochemical relapse-free survival, overall survival, and progression-free survival are the secondary outcome measures to preliminarily explore the optimal dose and efficacy of SIB carbon ion radiotherapy of localized prostate cancer.

Additionally, 25ml of peripheral blood and 35ml of urine will be collected prospectively before and after treatment for the detection of immune and circulating tumor cells related to prostate cancer carbon ion therapy. The purpose of these indicators’ detection is to evaluate the efficacy and toxicity of prostate cancer carbon ion therapy and then to predict the prognosis of the disease. Before the collection of biological specimens, an informed consent form will be provided by the principal investigator to patients.

Moreover, EQ-5D, IPSS, and EPIC questionnaires are used to evaluate the effect of carbon ion radiotherapy on patients’ quality of life. IPSS would be used to assess the lower urinary tract symptoms. EPIC would be used to evaluate the urinary, bowel, and sexual symptoms.

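### No between-arm comparison is stated for biochemical relapse-free, progression-free or overall survival, and their Kaplan-Meier estimates are planned for the two arms pooled

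*Protocol article*

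**What the plan says.** All quotations in this paragraph are from the Statistical analysis section of the protocol article. For the survival endpoints it states: "The Kaplan-Meier method will be used to estimate the biochemical relapse-free survival, progression-free survival, and overall survival of the entire cohort". On the use of log-rank it says: "The association between each of the candidate prognostic factors with biochemical relapse-free survival, progression-free survival, and overall survival rates will be tested". Then: "Multivariate analysis will be performed using the Cox regression model". The factors and the model covariates are not listed. The toxicity endpoints are treated differently: "The Mann-Whitney *U* test will be used to compare the differences in acute and late toxicity between the two arms". The section also sets the analysis population: "Analysis is planned on an intention-to-treat population (ITT), with all participants to be analyzed in the group to which they were randomized".

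On purpose, the Outcome measures section says the secondary endpoints serve "to preliminarily explore the optimal dose and efficacy of SIB carbon ion radiotherapy of localized prostate cancer". The Trial organization/coordination section gives the reasoning behind the boost: more tumour killing, and hence longer freedom from biochemical recurrence than standard treatment gives, at no cost in toxicity.

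**The concern.** A Kaplan-Meier curve that pools two randomised treatments estimates an average over the allocation mix and describes neither treatment. Log-rank tests of prognostic factors followed by a multivariable Cox model are the usual analysis of a single-cohort series. Neither one names the contrast that randomisation was set up to provide.

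At stake is the trial's own secondary question. If the survival section is followed to the letter, the report could contain a pooled survival figure and a table of prognostic factors, with no stated estimate of what the boost does to biochemical relapse-free survival. If an arm comparison is added later, it will look post hoc. The trial is open-label, so by-arm efficacy results could be seen before that comparison has been specified.

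**Working it through.** **1. The plan's own figure.** The only sample-size calculation is for acute toxicity. Its inputs, from the Statistical analysis section, are 90% in each arm, margin 0.15, type I error 0.025 (taken as one-sided) and power 80%.

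n per arm = (1.96 + 0.8416)² × (0.9×0.1 + 0.9×0.1) / 0.15² = 7.849 × 0.18 / 0.0225 = 62.8, so 63.

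With 10% dropout, 63 / 0.9 = 70 per arm, or 140 in total. The stated figures reproduce. They concern toxicity only and do not bear on this point. The article states no event count, hazard ratio or power for the survival endpoints.

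**2. What each planned analysis targets.**

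| Endpoint | Stated method | Stated target | Arm named? |
|---|---|---|---|
| Acute and late toxicity | Mann-Whitney | The two arms | Yes |
| Three survival endpoints | Kaplan-Meier | Whole cohort | No |
| Three survival endpoints | Log-rank | Prognostic factors, unlisted | No |
| Not stated | Cox | Covariates not named | No |

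The toxicity sentence shows that the authors name the arms when they intend an arm comparison. For survival, the Kaplan-Meier target is stated as the pooled cohort. That is a stated choice and goes beyond detail left open.

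**3. Set against the purpose.** The rationale is comparative, the Outcome measures section uses these endpoints to explore the boost's efficacy, and the intention-to-treat sentence presupposes that patients are analysed in their groups. A pooled curve fits none of the three.

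**4. What pooling hides (assumed values).** If relapse-free survival at some common time were 80% in one arm and 90% in the other, 1:1 pooling would report about (80 + 90) / 2 = 85%. The documents give no such rates.

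**5. How precise the arm comparison would be (assumed event counts).** With 1:1 allocation and d events, the standard error of the log hazard ratio is about 2/√d. The 95% limits are therefore the estimate divided and multiplied by exp(1.96 × 2/√d):

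- d = 10: exp(1.240) = 3.45
- d = 30: exp(0.716) = 2.05

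For power, take two-sided 0.05 (also assumed) and the Schoenfeld formula. The events needed for 80% power are 4 × 7.849 / (ln HR)², which gives 66 at a hazard ratio of 0.5, 121 at 0.6 and 247 at 0.7. Power at fixed event counts is:

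| Events | HR 0.5 | HR 0.6 | HR 0.7 |
|---|---|---|---|
| 20 | 34% | 21% | 12% |
| 40 | 59% | 37% | 20% |

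With 140 patients and a stated minimum of 3 months' follow-up (Duration of the study), the events needed for a confirmatory test are unlikely. The useful output is an estimate with its interval.

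**The case against.** **Arm may already be included.** The factors and Cox covariates are not listed, and nothing excludes arm from either. The intention-to-treat sentence also points towards analysis by group. This stands as far as it goes, so a reader who infers that the plan rules out or never makes an arm comparison goes beyond the text. It does not remove the point. The intention-to-treat sentence names no efficacy contrast. Even if arm is one of the factors, the randomised comparison would be one unranked test among an unknown number, and the Kaplan-Meier estimates would still be pooled.

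**The full protocol or an analysis plan may settle it.** The missing lists of factors and covariates are indeed no fault of a journal article. The Kaplan-Meier target, however, is stated. A fuller document with by-arm curves would depart from the published wording, which would need correcting in either case.

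**The endpoints are exploratory.** This is true, and it limits the weight of the point. A reader might infer that the trial cannot meet its secondary objective. The documents do not support that: the aim is only preliminary exploration, no efficacy hypothesis is powered, allocation is known for every patient, and the comparison can still be specified. Late toxicity, itself a secondary outcome, is already compared between arms.

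**The comparison would be imprecise.** It would, but that is a reason to report an interval and does not justify leaving the contrast unstated.

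**Conclusion.** The point holds in a limited form. The article fixes pooled Kaplan-Meier estimates for the three survival endpoints and states no between-arm efficacy comparison, which sits badly with its comparative rationale, its stated use of these endpoints and its intention-to-treat sentence. It should be fixed, but it is not critical: the primary toxicity comparison, the late-toxicity comparison and the sample size are untouched.

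No numerical error can be attached to it, because the defect is one of wording. The survival percentages, event counts, hazard ratios and two-sided 0.05 level in the working are assumptions chosen to show scale. The conclusion depends on none of them, only on the text.

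**What to change.** In the Statistical analysis section:

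- Replace the whole-cohort Kaplan-Meier target with estimates by randomised arm in the intention-to-treat population.
- State an exploratory comparison of arm B with arm A for each of the three survival endpoints: a log-rank test and a Cox hazard ratio with 95% confidence interval. Say that interpretation rests on the estimate and its interval, because events will probably be few.
- Keep the pooled prognostic-factor analysis, labelled supplementary.

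Adjustment for risk group is optional and should depend on the number of events. The target-volume section names four risk groups, so a model with arm would have 1 + 3 = 4 parameters. At an assumed 10 events that is 10 / 4 = 2.5 events per parameter, which would be unstable.

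The cost is a few sentences, a little analysis code and a formal amendment through the Institutional Review Board, which the Protocol amendments section requires for changes to analyses. No new data are needed. The change should be made before efficacy results by arm are examined.

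### The plan permits last observation carried forward for the primary acute toxicity endpoint of a non-inferiority trial, where it can only undercount events

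*Protocol article*

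**What the plan says.** The Statistical analysis section of the protocol article sets the trial up as a non-inferiority comparison: "Assuming a type I error of 0.025 and type II error of 0.2", the same 90% rate assumed in both arms, "with a non-inferiority margin of 0.15", and the conclusion that "a sample size of 63 participants per arm will yield 80% power to show non-inferiority". Allowing for 10% dropout, this becomes 70 per arm and 140 in total.

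The same section states: "Analysis is planned on an intention-to-treat population (ITT), with all participants to be analyzed in the group to which they were randomized". Patients who leave early therefore stay in the analysis and need an outcome. For them, "the missing data will be dealt with last observation carried forward method or multiple imputation". Nothing in the article says which of the two methods applies to the primary endpoint, or under what conditions.

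The Abstract and the Duration of the study section give the primary endpoint as the incidence of treatment-related acute toxicity of grade 2 or higher. Treatment lasts 4 weeks (Definition of the dosage). Table 1 schedules acute toxicity grading before treatment, weekly during it, on its last day, at weeks 4–6 and at month 3. The trial is open-label (Trial organization/coordination).

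**The concern.** The endpoint asks whether a patient ever reaches grade 2 during a window that runs for weeks beyond the last fraction. A patient who leaves at grade 0 or 1 has an unknown outcome. LOCF turns that unknown into a definite non-event, because it assumes no later worsening. The error runs one way: LOCF can miss an event but cannot create one.

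In a superiority trial such undercounting would usually cost power. Here, if the boost arm is truly more toxic and loss is similar in the two arms, losing the same share of events from each arm reduces the absolute difference. That makes it easier to fall below the margin. At stake is the protection that the stated type I error is meant to give against declaring a more toxic treatment acceptable.

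The unresolved choice adds to this. In an open-label trial, a method that is not fixed beforehand can be picked once outcomes are known, and one of the two candidates leans towards the desired conclusion.

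**Working it through.** **The plan's own figure.** Inputs from the Statistical analysis section: rate 0.90 in both arms, margin 0.15, type I error 0.025 (sidedness not stated; taken as one-sided), power 0.80.

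n per arm = (1.960 + 0.842)² × (0.9×0.1 + 0.9×0.1) / 0.15² = 7.849 × 0.18 / 0.0225 = 62.8, so 63. With dropout, 63 / 0.9 = 70. Both figures reproduce, so the sample size is not at issue.

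**Set-up for the error rate.** The 90% is read as the proportion free of the primary event, so arm A has a 10% event rate. A true arm B rate 0.15 higher, 25%, puts the trial exactly at the margin. Any conclusion of non-inferiority there is false. With 70 per arm, non-inferiority is declared when the upper limit of the two-sided 95% interval for the difference (B minus A) is below 0.15. The article does not name an interval, so two are used, Newcombe and Wald. The probabilities come from exact enumeration of all binomial outcomes.

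**Effect of LOCF.** Let d be the proportion lost in each arm and u the share of lost patients' events that have not yet occurred when they leave. If lost patients have the same underlying risk as the others, the observed rate is the true rate × (1 − d×u). The value d = 10% is the plan's dropout figure. The value of u is not in the document, so a range is shown.

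| u | Observed A | Observed B | Observed difference | False non-inferiority, Newcombe | Wald |
|---|---|---|---|---|---|
| 0 | 10.0% | 25.0% | 15.00 points | 2.5% | 2.9% |
| 0.5 | 9.5% | 23.75% | 14.25 points | 3.3% | 3.8% |
| 1 | 9.0% | 22.5% | 13.50 points | 4.3% | 5.0% |

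**Hand check of the last row by normal approximation.** Standard error = √[(0.09×0.91 + 0.225×0.775)/70] = 0.0605. Then (0.15 − 0.135)/0.0605 − 1.960 = −1.712, and Φ(−1.712) = 4.3%. For u = 0.5 the same formula gives 3.3%.

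**The case against.** The strongest reply is that little of this will occur in practice. The Patient assessments section requires acute toxicity to be graded at least weekly during irradiation and until it subsides. The section on retention has patients stay on site until discharge, requires those who withdraw for adverse events to be followed to recovery or stabilisation, and continues toxicity follow-up when treatment is incomplete for reasons other than progression. A patient who leaves because of toxicity has that toxicity on record, and an event once seen stays counted. This stands. It makes u = 1 an upper illustration and not an expectation. It does not remove the problem, because the plan itself allows for 10% dropout, and patients who leave for other reasons can be lost before the visits at weeks 4–6 and month 3.

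It can also be said that a statistical analysis plan, not shown here, may settle the method. It may, but LOCF is expressly allowed in the article and is not merely left unmentioned.

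Three stronger readings are not supported:

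- A reader might infer that the primary analysis rests on LOCF. It does not; multiple imputation is named beside it.
- A reader might infer that intention-to-treat as the only named population is itself a flaw, because arm B patients without the boost would dilute a difference. A per-protocol set is commonly left to the full protocol or the analysis plan. The boost is delivered within the same 16 fractions as the rest of the dose, and eligibility requires a visible lesion, so any rate of non-receipt would be pure assumption.
- A reader might assume heavier loss in arm B. Losing 10% of events in arm A and 20% in arm B would give 9.7% (Newcombe) to 11.3% (Wald), but nothing in the document supports such a differential. Loss concentrated in arm A would work the other way.

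**Conclusion.** The concern holds in a limited form. LOCF is a poor option for this endpoint because its error has one direction, and under similar loss in both arms that direction favours non-inferiority. The article also leaves open whether it will be used. If LOCF were used with 10% loss in each arm, the false non-inferiority rate at the margin would lie between its nominal value and 4.3% (Newcombe) or 5.0% (Wald), depending on how many dropouts leave before any event.

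These figures assume equal loss in both arms, dropouts with the same underlying risk as completers, an event defined as grade 2 or higher, and a confidence-interval test of the risk difference. The last is an assumption because the only toxicity test that the article names is Mann-Whitney U. The direction of the bias needs less: only that some patients are lost before a first event, that loss is not concentrated in arm A, and that arm B is truly more toxic.

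The effect is modest and easily removed. It does not invalidate the design.

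**What to change.** Delete LOCF for the acute toxicity endpoint. State, before any comparison by arm, that multiple imputation is the primary method for patients with an incomplete acute window and no event yet. The imputation model should include arm, risk group, baseline scores and the last observed grade. Patients with an event already recorded keep it and need no imputation.

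Multiple imputation assumes that missing outcomes can be predicted from what was recorded. Add a tipping-point sensitivity analysis that assigns progressively higher event rates to missing arm B patients and reports where the conclusion changes.

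Keep that analysis supportive and do not make it a condition for concluding non-inferiority. Its extreme form counts missing arm B patients as events and missing arm A patients as non-events. With 10% missing and both arms truly at 10%, the expected rates would be 0.9 × 10% = 9% in arm A and 0.9 × 10% + 10% = 19% in arm B. Non-inferiority would then be shown only about 13% (Newcombe) to 15% (Wald) of the time, although the arms are equal.

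The cost is a short wording change, slightly more analysis work and a non-inferiority claim that is slightly harder to reach. No extra patients are needed.
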